## Power Calculations

The table shows a range of sample sizes needed to achieve a power of 0.8-0.9 with an effect size of 25% to 50% improvement in MS-MFR (an improvement of 25% would be deemed clinically significant). A sample size of 20 would achieve at least 80% power with an effect size of 25%. Because some patients may drop out, we plan to increase the sample size by 20%, bringing the final sample size to 24, with 16 in the Biofeedback group and 8 in the Control group.

Table. Sample size determination and power.  
(BF=Biofeedback, C=Control)

| BF Group
MFR | Control
Group MFR | SD  | Power | Improvement in MS-
MFR | Total n |
|-----------------|----------------------|-----|-------|---------------------------|---------|
| 1.38            | 1.1                  | 0.2 | 0.8   | 25%                       | 20      |
| 1.65            | 1.1                  | 0.2 | 0.8   | 50%                       | 8       |
| 1.38            | 1.1                  | 0.2 | 0.9   | 25%                       | 26      |
| 1.65            | 1.1                  | 0.2 | 0.9   | 50%                       | 10      |

## Adverse event reporting

All adverse events (AEs) will be graded as to their attribution (unrelated to protocol, or possibly, probably, or definitely related to protocol). Any AE that is reported by a study subject or by medical staff caring for the subject and which meets the criteria will be documented as such.

Serious adverse events (SAEs) are defined as: any experience that suggests a significant hazard, such as events which: a) are fatal, b) are life threatening, c) result in persistent or significant disability, d) requires or prolongs inpatient hospitalization, e) results in congenital anomalies/birth defects, or f) in the opinion of the investigators represents other significant hazards or potentially serious harm to research subjects or others. In the case of a severe adverse event a code will be called to access immediate emergency medical attention. This adverse event

will be immediately communicated to the research coordinator. Any SAE will be reported to the PI and the IRB within 24 hrs.

Unanticipated problems (UPs) are defined as unanticipated events involving risks to participants or others that are possibly, probably, or definitely related to the research; or anticipated events that occur with a greater frequency, duration, or severity than what is documented in the protocol, informed consent, or investigator's brochure; or other unanticipated information that changes the risk benefit ratio or that indicates participants or others might be at greater risk of harm than was previously known. SAEs and UPs are to be reported to the supervising institutional IRB and sponsor as per their policies and procedures.

The investigators and staff will track and summarize AE frequency, severity, and relatedness at a frequency appropriate to insure subject safety.

Potential ("expected") adverse events and plan for detecting problems and minimizing subject risk during this trial: (1) PET radiation exposure, (2) intravenous catheter, (3) blood draw, (4) mental stress test, (5) inconvenience of wearing EKG leads.

Expected adverse events will be detailed in the Consent Form and include the following: (1) PET radiation exposure, (2) intravenous catheter, (3) blood draw, (4) mental stress test, (5) inconvenience of wearing EKG leads.

Procedures for minimizing risks: (1) A radiation exposure history will be obtained from each subject prior to their being exposed to the PET scan. Every effort will be made to keep the exposure to a minimum. (2) Medication can be given prior to the PET scan to help with apprehension and anxiety if necessary. A physician will be present throughout the procedure and vital signs and heart rate will be monitored while the Rb dose is infusing. (3) Every effort will be made to insert the IV catheter and perform blood draws as painlessly as possible on the first attempt. (4) Immediately after the mental stress test, study staff will debrief subjects; if necessary the study psychiatrist will see the patient and take further action. Patients who become suicidal will be escorted to the emergency room. Arrangements for treatment referral will be made during the course of the study if necessary. (5) The adhesive back of the monitor leads could cause some irritation to the skin. The irritation can be relieved by hydrocortisone cream and will usually disappear in 1-2 days even with no treatment.

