## **Introduction and Background**

There is growing recognition of the detrimental effects of psychological and emotional stress on coronary heart disease (CHD) incidence and mortality. Psychological stress has been implicated in the pathophysiology of CHD by triggering acute coronary events, exacerbating CHD risk factors, influencing development of atherosclerosis, and impairing the recovery, prognosis and quality of life of patients after an acute coronary syndrome. In up to half of patients with CHD, myocardial ischemia can be induced by a standardized psychological challenge. This mental-stress induced myocardial ischemia (MSI) is analogous to exercise stress ischemia, except that the stimulus is psychological rather than physical or pharmacological stress. It is typically painless, occurs at lower levels of oxygen demand than exercise ischemia, is generally not related to severity of coronary artery disease (CAD), and is a predictor of poor prognosis. However, the exact mechanisms underlying MSI and its adverse prognostic significance are unknown. One proposed mechanism is reduced coronary perfusion secondary to impaired vasodilation of the coronary circulation during mental stress that may primarily be an abnormality of the coronary microcirculation. Patients with CAD who develop MSI appear to be especially vulnerable to psychological stress and thus represent an ideal group to study the effects of intervention on myocardial perfusion changes during psychological stress.

Peripheral or pulsatile arterial tonometry (PAT) is a vascular test developed to evaluate digital microvascular vasodilator function in the fingertip. PAT reactive hyperemia predicts short and long term risk of cardiovascular events. We have shown that patients with CAD who do not develop MSI during laboratory psychological testing have significantly greater digital vasodilation, measured using PAT, than patients with MSI.

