**Before Mental Stress Testing:** Patients will be studied in the morning after an overnight fast. After consent, patients will have 20 ml blood drawn for measurements of catecholamine levels, and inflammatory markers. They will be outfitted with a combined ECG/ICG monitor, the VU AMS holter, which is a 5-lead recorder that measures cardiac impedance and ECG for the autonomic measures. Additionally, they will measure a fitness bracelet, the Empatica E4, to measure photoplethysmography and actigraphy. In a quiet temperature controlled Vascular Laboratory, after at least 15 minute rest period, we will measure arterial compliance (augmentation index and pulse wave velocity) using the SphygmaCor device. Immediately following this, patients will be fitted with the tonometry device (PAT, Itamar Inc), and we will measure endothelial function by brachial artery reactivity testing and simultaneously also measure PAT reactive hyperemia index. Once this test is completed within 15 to 20 minutes, patients will be moved to the PET laboratory for a 30-minute rest period before the mental stress test. During this period, heart rate and blood pressure will be measured at every 5 minutes (automatic oscillometric device (Datascope Accutorr) and a continuous recording of microvascular finger blood flow using the PAT device will continue. They will continue to wear the VU AMS device and Empatica bracelet, and also undergo additional 12-lead ECG monitoring during the stress to evaluating for arrhythmia/ST changes. The resting study

Rubidium^82 infusion and PET image acquisition will be obtained approximately 7.5 mins prior to mental stress. 30-60 mCi of Rubidium^82 (based on patient body weight) will be injected in total.

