### **Adherence Assessment**

The biofeedback coach will instruct participants in both groups to practice their training at home a minimum of 10 minutes a day, and a goal of 20 minutes per day. Participants will be given a log to record their daily home practice. Home practice self-report data will be incorporated into the analysis to examine the potential dose-response effects of home practice. Information will be solicited in a questionnaire at the start of each lab regarding the factors that contributed to or detracted from home practice, for inclusion in the analysis. One goal of this intervention is to spontaneously and consistently achieve HRV coherence on demand outside a clinical environment. Therefore, participants will be provided with a portable colorimetric finger PPG hand held personal stress reliever; dimensions similar to a cell phone; weight: 2.2 ounces for home practice and use between weekly HRVB training sessions. Home HRVB practice period data from the device can be compared to self-report and further analyzed with regard to the outcomes.

Personal HRVB coaching will be provided by HRVB trainer/mentors. These individuals are trained to teach the practical application of HRVB. Three individual mentoring sessions per participant will be provided via telephone or online via Skype to supplement acquisition of core HRVB skills through home practice. Through this program, the methods of achieving and sustaining HRV coherence are reinforced.

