## **Stopping Rules for Study**

### Absolute indications for study wide termination (determined by the PI)

- the intervention is associated with adverse effects that call into question the safety of the intervention
- difficulty in study recruitment or retention that will significantly impact the ability to evaluate the study endpoints
- any new information becomes available during the trial that necessitates stopping the trial
- other situations occur that might warrant stopping the trial

Plans for transmission of temporary or permanent suspension actions: Any actions that mandate temporary or permanent suspension of study will be transmitted to the institutional IRB, and, if appropriate, to the study sponsor, FDA, or the National Institutes of Health.

Plans for protecting subject confidentiality: All information and materials that are obtained for research purposes only will be kept in strict confidence. Confidentiality will be assured by the

use of subject codes rather than personal identifiers. No names will be used on study forms. A crosswalk linking will be kept under lock and key in another location. After the study is completed, the crosswalk will be destroyed. The study database will be secured, and information will only be entered using subject identifier codes rather than personal identifiers. Electronic communication will involve only coded, unidentifiable information.

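### Adverse events are captured by report, with no common scheduled question, while between-visit contact differs by arm in weeks 0-6, so recorded events can differ by arm through ascertainment alone

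*Protocol*

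**What the plan says.** The Adverse event reporting section states one capture rule. It covers "Any AE that is reported by a study subject or by medical staff caring for the subject", and such an event is documented if it meets the criteria. The section defines serious events and unanticipated problems, but not the criteria that an ordinary adverse event must meet. On follow-through it adds: "The investigators and staff will track and summarize AE frequency, severity, and relatedness at a frequency appropriate to insure subject safety". It names no standard question, look-back period or schedule of enquiry.

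On contact, the Adherence Assessment section gives participants a hand-held device "for home practice and use between weekly HRVB training sessions", and adds: "Three individual mentoring sessions per participant will be provided via telephone or online via Skype". The Biofeedback Intervention Protocol has an off-site trainer conduct half of the sessions by phone. The Abstract starts biofeedback after enrolment in the intervention arm, and between the week-6 and week-12 visits in the wait-list arm.

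On use, the first criterion under Stopping Rules for Study, which the PI determines, is that "the intervention is associated with adverse effects that call into question the safety of the intervention".

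On observation during testing, patients "undergo additional 12-lead ECG monitoring during the stress to evaluating for arrhythmia/ST changes", and a separate section lists criteria for ending the mental stress test.

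**The concern.** A rule driven by reports records an event only if someone raises it. The number of occasions to raise it then matters, and in weeks 0-6 those occasions are not the same in the two arms. A participant in weekly conversation with a trainer has repeated chances to mention a symptom. The Adherence Assessment section also solicits, by questionnaire, factors that got in the way of home practice, and symptoms can surface there. A wait-list participant has no described study contact until week 6. A wait-list comparison cannot be masked to participants, so knowledge of the arm may also affect what is reported.

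What is at stake is the safety judgement on biofeedback. The PI must decide whether adverse effects are associated with the intervention, and the Data Safety Monitoring Plan treats the study as one that does not need a DSMB. The definition of an unanticipated problem also depends partly on whether expected events occur more often than documented. Both judgements need counts gathered in the same way in each arm.

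A smaller gap concerns events that staff see for themselves. The protocol does not say whether an ECG change, or a met criterion for ending the stress test, is entered as a safety event.

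**Working it through.** The protocol states no adverse event rate, count or calculation, so there is no figure to reproduce. The check sets the sections side by side and then illustrates the mechanism on assumed values.

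**Step 1. How an event enters the record.** The source named is a report by the subject or by caring medical staff. The sentence on tracking covers how often events are summarised, not how they are elicited. The debrief after each stress test (procedures for minimizing risks) leads to psychiatric review if needed and is not described as event collection.

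**Step 2. Contact between visits.** The number of sessions is not stated. One session a week for six weeks (assumed) gives 6. The three mentoring sessions may be the remote half of those (6 / 2 = 3) or additional to them (6 + 3 = 9).

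| Period | Biofeedback arm | Wait-list arm |
|---|---|---|
| Weeks 0-6, between visits | 6 to 9 contacts | none described |
| Weeks 6-12, between visits | none described | 6 to 9 contacts |
| Week-6 and week-12 visits | yes | yes |

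The imbalance reverses after week 6, when the wait-list arm is treated. Totals over 12 weeks therefore do not contrast treated with untreated participants.

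**Step 3. Effect on recorded risk (illustration).** Recorded risk = true risk × capture probability. With equal true risks, the apparent risk ratio is capture (biofeedback) / capture (wait-list). Assume a true risk of 20% in both arms and 90% capture with weekly contact:

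| Wait-list capture (assumed) | Recorded, biofeedback | Recorded, wait-list | Ratio |
|---|---|---|---|
| 50% | 0.20 × 0.90 = 18% | 0.20 × 0.50 = 10% | 1.8 |
| 70% | 18% | 0.20 × 0.70 = 14% | 1.29 |
| 90% | 18% | 0.20 × 0.90 = 18% | 1.0 |

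The ratio does not depend on the 20%. Under these assumptions any error in weeks 0-6 makes biofeedback look worse. The lower end is no bias at all.

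**Step 4. Why denominators are needed.** Overall Study Design gives 1:1 allocation; Power Calculations gives 16 and 8. With equal capture and equal risk, 16:8 alone would yield twice as many raw events under biofeedback: 16 × 0.18 = 2.88 against 8 × 0.18 = 1.44. Counts without denominators would add this to any ascertainment effect.

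**The case against.** The strongest reply has four parts.

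- **The rule is inclusive.** It does not say that other sources are excluded. Staff track events, meet weekly or every two weeks, and debrief subjects after each stress test. This stands against any claim that events are recorded only on a report. It does not supply a common question or schedule.
- **No between-arm comparison of adverse events is planned.** The Statistical analysis section compares myocardial blood flow and flow reserve. The stopping rule is a PI judgement without a numerical threshold, and each event is graded for attribution. The listed expected events arise from visit procedures, which do not depend on contact between visits. This limits the consequence. Still, judging whether adverse effects are associated with the intervention implies some comparison, even if informal.
- **Trainers are not named as event collectors.** More coaching contact need not mean more capture, so the most that can be said is that counts can differ, not that they do. One sentence in Adherence Assessment has the coach instruct both groups, but the Abstract places the wait-list arm's training after week 6, so the imbalance in weeks 0-6 remains.
- **Tabulation belongs in the analysis plan, and the data forms are not at hand.** That is fair for table layouts. How events are elicited is a protocol matter, and here the protocol states a rule.

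A reader might go further and infer that silent ischemia during testing escapes the record, because the Introduction says of mental-stress ischemia: "It is typically painless, occurs at lower levels of oxygen demand than exercise ischemia". One could even apply that section's upper figure of one half to 24 × 2 = 48 imaging sessions and arrive at 24 unrecorded events. The protocol does not support this. Ischemia during testing is measured in both arms by PET at baseline and week 6, and the number of ischemic regions is a secondary outcome. ECG is monitored during stress, with a physician present throughout the PET procedure. The 24 would be measured outcomes, not missed harms. Nor would a question to patients reveal painless ischemia.

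**Conclusion.** The point holds in a limited form. Event capture rests on reports, no common scheduled enquiry is set, and between-visit contact differs by arm in weeks 0-6 in a trial that participants know is unmasked. Ascertainment can therefore differ by arm and feed into the PI's stopping judgement.

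The size is unknown. The apparent ratio of 1.8 to 1.0 rests wholly on assumed capture probabilities, and the contact count of 6 to 9 assumes one session a week for six weeks. In a 24-patient pilot without a planned test on adverse events, this is a modest weakness with a cheap remedy. It does not show that events are biased, or that ischemia goes undetected. On ischemia and arrhythmia, the remaining gap is narrow: the text does not link what staff already observe to the safety record.

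**What to change.** In Adverse event reporting:

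1. Ask every participant in both arms the same open question about adverse events at the existing baseline, week-6 and week-12 visits, and record the onset date.
2. Base any between-arm summary on events elicited at visits and arising in weeks 0-6, with the number of participants per arm as denominator.
3. List coach-reported events separately, and likewise events from weeks 6-12, when the wait-list arm also receives biofeedback.
4. State that ECG events and met termination criteria already observed by staff during stress testing are entered in the safety log, by arm and visit. The criteria themselves stay unchanged.

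The cost is protocol and form wording, one question at visits that already take place, and tabulation of observations already made. More minor events will be recorded. Recall over six weeks is imperfect and coaching may still prompt memory, so the change reduces unequal ascertainment rather than removing it.

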#### **Data Safety Monitoring Plan (DSMP)**

The Data Safety Monitoring Plan (DSMP) outlined below will adhere to the protocol approved by the institutional IRB responsible for study oversight. An IRB-approved written informed consent will be obtained from each subject at entry into the study; elements of informed consent will include: (a) having the subject review the study consent form; (b) having the investigator(s) or study staff meet with the subject to review the consent, confirm understanding, and answer any questions; and (c) once the investigator(s) or study staff are convinced that the protocol is understood and that there is agreement to participate, having the consent signed. A copy of the signed consent form will be provided to subject and/or their legally authorized representative. Documentation of the informed consent process will be made in the research and/or medical records as appropriate. The principal investigator (PI) will review all data collection forms for completeness and accuracy of the data as well as protocol compliance. Any data inconsistencies will be resolved by study staff as soon as possible. The PI will review this protocol on a continuing basis for subject safety and protocol deviations or study noncompliance. Reportable

Events will be communicated to the local institutional IRB as required. The results of the review will also be included in progress reports submitted to the local institutional IRB, or any other regulatory agency or sponsor, as required.

## **Stopping Rules for Mental Stress Testing.**

### Absolute Indications for Termination

- ST-segment elevation (>1.0 mm) in leads without Q waves (other than V1 or aVR).
- Drop in systolic blood pressure >10 mm Hg (persistently below baseline), despite an increase in workload, when accompanied by any other evidence of ischemia.
- Moderate-to-severe angina at a level that the patient wishes to stop.
- Central nervous system symptoms (eg, ataxia, dizziness, or near syncope).
- Signs of poor perfusion (cyanosis or pallor).
- Sustained ventricular tachycardia.
- Technical difficulties monitoring the ECG or systolic blood pressure.
- Subject's request to stop.

### Relative Indications for Termination

- ST or QRS changes such as excessive ST displacement (horizontal or downsloping of >2 mm) or marked axis shift.
- Drop in systolic blood pressure >10 mm Hg (persistently below baseline) despite an increase in workload, in the absence of other evidence of ischemia.
- Increasing chest pain.
- Fatigue, shortness of breath, wheezing, leg cramps, or claudication.
- Arrhythmias other than sustained ventricular tachycardia, including multifocal ectopic, ventricular triplets, supraventricular tachycardia, heart block, or bradyarrhythmias.
- General appearance (see below).
- Hypertensive response (systolic blood pressure >250 mm Hg)
- Development of bundle-branch block that cannot be distinguished from ventricular tachycardia.
- If the patient becomes excessively anxious or uncomfortable, or requests us to stop.

## **Stopping Rules for Study**

### Absolute indications for study wide termination (determined by the PI)

- the intervention is associated with adverse effects that call into question the safety of the intervention
- difficulty in study recruitment or retention that will significantly impact the ability to evaluate the study endpoints
- any new information becomes available during the trial that necessitates stopping the trial
- other situations occur that might warrant stopping the trial

Plans for transmission of temporary or permanent suspension actions: Any actions that mandate temporary or permanent suspension of study will be transmitted to the institutional IRB, and, if appropriate, to the study sponsor, FDA, or the National Institutes of Health.

Plans for protecting subject confidentiality: All information and materials that are obtained for research purposes only will be kept in strict confidence. Confidentiality will be assured by the

use of subject codes rather than personal identifiers. No names will be used on study forms. A crosswalk linking will be kept under lock and key in another location. After the study is completed, the crosswalk will be destroyed. The study database will be secured, and information will only be entered using subject identifier codes rather than personal identifiers. Electronic communication will involve only coded, unidentifiable information.

Plans for assuring data accuracy and protocol human safety compliance: An IRB-approved written informed consent will be obtained from each subject at entry into the study; elements of informed consent will include: (a) having the subject review the study consent form; (b) having the investigator(s) or study staff meet with the subject to review the consent, confirm understanding, and answer any questions; and (c) once the investigator(s) or study staff are convinced that the protocol is understood and that there is agreement to participate, having the consent signed. A (bi)weekly meeting with the staff, Study Coordinator and the PI is held to discuss any issues that may arise. A review of data collection forms is done for accuracy and protocol compliance. Data collection forms are scanned and verified for accuracy before storing in database. The PI will review this protocol on a continuing basis for subject safety and include the results of the review in annual progress reports submitted to the IRB. Patient Monitoring: will be performed by the PI, the Co-Investigators, and the Research Coordinator(s). Any unanticipated events are reported to the IRB in a timely manner per protocol.

The above detailed plans should assure data accuracy and protocol human safety compliance for this study. These include computerized database management, and IRB oversight and communication. This plan, together with oversight by the IRB, should be sufficient for studies that do not require a DSMB.

